### 6.3.2 Data collection

Data will primarily be collected through the app as self-reported answers to questionnaires and as analytics. The Case Report Form in supplement 6 shows the questions and response alternatives for each instrument. Table 1 shows an overview of time points and instruments used for data collection.

#### *Reach*

Information on promotion channels and data on sales statistics will be collected from the provider. This data is not connected to the subjects. Demographics: age, gender, occupational status, profession, education, country of origin and living area, as well as a question on how the subject got information about the service will be collected by questions when signing up.

#### *Fidelity and dose*

User activity patterns across time will be aggregated per week and described for the core functions: *Individual action plan, Coaching, Community and Platform of knowledge and inspiration*. Adherence with app use will be estimated using the frequency of weekly use across the tracking period. Supplement 6 Case Report Form shows the variables to be collected for this purpose.

#### *Adaptations*

Qualitative data from the support service chat, and from continuous dialogues with health coaches, recipe providers and staff maintaining the digital service and records over notable adaptations and changes made to the service will continuously be collected. Details and routines are described in the IB (Supplement 4).

#### *Usability*

Perceived usability of the service will be collected by the System Usability Scale (SUS) (31) and acceptability by Mobile Application Rating Scale Instrument for Evidence-Based Evaluation (MARS), (30).

### *Mediating factors and mechanisms of impact*

Motivation will be assessed by the readiness to change questionnaire (RTCQ) based on the transtheoretical model (37, 38). Self-efficacy will be evaluated by the General Self-Efficacy scale (S-GSE) adapted for behaviour change (39). Barriers to healthy behavior will be evaluated by the Barriers to being active quiz (CDC Road to health barriers) adapted for barriers in trying to eat healthier and to recover (40).

### *Outcome measures*

#### *Mental health*

Well-being will be assessed by the WHO-5 Well-Being Index (34). The WHO-5 comprises the following five items: being cheerful and in good spirits; being calm and relaxed; feeling active and vigorous; feeling fresh and rested when waking up in the morning; and having an interest in day-to-day activities. Six response alternatives are scored from 5 (All of the time) to 0 (At no time). The total raw score which ranges from 0 to 25 is multiplied by 4 to calculate the final score. The final score range goes from 0 = worst imaginable well-being to 100 = the best imaginable well-being. Stress will be assessed by the Karolinska Exhaustion Disorder Scale, a self-rating scale for stress-induced exhaustion disorder (41). Burnout will be assessed by the Oldenburg Burnout Inventory (OLBI) (42). Sleep will be assessed by the self-reported number of hours of sleep per night and ISI – Insomnia Severity Index (43). Four questions have been developed specifically for this study to assess mental balance.

#### *Goal achievement*

Reaching the self-identified goal will be evaluated by collecting information on number of days/week the self-identified goal was met during the past month. Confidence for reaching the goal will also be asked for on a scale 1 low confidence to 6 high confidence.

#### *Dietary habits*

Dietary behaviours will be assessed by questions from the Social Board of Health and Welfare (44), with the addition of some study specific questions on plant based diet.

#### *Physical activity and sedentary behaviors*

Physical activity and sedentary behaviors will be collected by questions from the Social Board of Health and Welfare (44) with additional questions on active transport and physical activity at work. In a randomized sample of individuals having increased physical activity as a goal (n=300) physical activity will also be measured objectively by the use of the three-axial accelerometer-based device Fibion (Fibion Inc, Jyväskylä, Finland) (45) or a similar device. Daily number of steps will be obtained from app analytics.

| Aspect                       | Variable                                                         | Instrument                                      | Time point (month) |   |   |   |    |    |    |
|------------------------------|------------------------------------------------------------------|-------------------------------------------------|--------------------|---|---|---|----|----|----|
|                              |                                                                  |                                                 | 0                  | 1 | 3 | 6 | 12 | 18 | 24 |
| Demographics                 |                                                                  |                                                 |                    |   |   |   |    |    |    |
|                              | Age                                                              | Year of birth                                   | x                  |   |   |   |    |    |    |
|                              | Gender                                                           | SCB                                             | x                  |   |   |   |    |    |    |
|                              | Occupation                                                       | No specific                                     | x                  |   |   |   |    |    |    |
|                              | Profession                                                       | No specific                                     | x                  |   |   |   |    |    |    |
|                              | Education                                                        | No specific                                     | x                  |   |   |   |    |    |    |
|                              | Living area                                                      | No specific                                     | x                  |   |   |   |    |    |    |
|                              | Country of origin                                                | No specific                                     | x                  |   |   |   |    |    |    |
| Well-being and mental health |                                                                  |                                                 |                    |   |   |   |    |    |    |
|                              | Well-being                                                       | WHO-5 Well-being index                          | x                  | x | x | x | x  | x  | x  |
|                              | Stress                                                           | The Karolinska Exhaustion Disorder Scale (KEDS) | x                  |   | x | x | x  | x  | x  |
|                              | Burnout                                                          | The Oldenburg Burnout Inventory (OLBI)          | x                  |   | x | x | x  | x  | x  |
|                              | Sleep                                                            | Self-reported number of hours at sleep          | x                  |   | x | x | x  | x  | x  |
|                              |                                                                  | Sleep diary*                                    |                    |   |   |   |    |    |    |
|                              |                                                                  | ISI – Insomnia Severity Index                   | x                  |   | x | x | x  | x  | x  |
|                              | Mental balance                                                   | No specific                                     | x                  |   | x | x | x  | x  | x  |
| Goal achievement             |                                                                  |                                                 |                    |   |   |   |    |    |    |
|                              | Confidence in reaching the goal                                  | No specific                                     | x                  |   | x | x | x  | x  | x  |
|                              | Days/week the self-identified goal was met during the past month | Analytics                                       | x                  | x | x | x | x  | x  | x  |
| Mediators                    |                                                                  |                                                 |                    |   |   |   |    |    |    |
|                              | Self-efficacy                                                    | The General Self-Efficacy scale (S-GSE)         | x                  |   | x | x | x  | x  | x  |

|                                                      |                                                                                                            |   |   |   |   |   |   |
|------------------------------------------------------|------------------------------------------------------------------------------------------------------------|---|---|---|---|---|---|
| Motivation                                           | Readiness to change questionnaire (RTCQ)                                                                   | x | x | x | x | x | x |
|                                                      |                                                                                                            |   |   |   |   |   |   |
| Barriers                                             | CDC Road to health barriers                                                                                | x | x | x | x | x | x |
| Lifestyle habits                              |                                                                                                            |   |   |   |   |   |   |
| Physical activity                                    | Daily number steps from the app**                                                                          | x | x | x | x | x | x |
|                                                      | Daily minutes in different intensities and sedentary behavior                                              | x |   |   | x | x | x |
|                                                      | Questions from the National Board of Health and Welfare on active transport and physical activity at work. | x |   |   | x | x | x |
| Dietary habits                                       | Questions from the National Board of Health and Welfare and additional questions on plant-based food.***   | x |   |   | x | x | x |
| Usability                                     |                                                                                                            |   |   |   |   |   |   |
| Usability                                            | System Usability Scale (SUS)                                                                               |   | x | x |   |   |   |
| Acceptability                                        | Mobile Application Rating Scale (MARS)                                                                     |   | x | x |   |   |   |
| Engagement                                    |                                                                                                            |   |   |   |   |   |   |
| Use of action plan                                   | Analytics                                                                                                  | x |   | x | x | x | x |
| Attendance at community tutorials och coaching       | Analytics                                                                                                  | x |   | x | x | x | x |
| Number visits at knowledge and inspiration databases | Analytics                                                                                                  | x |   | x | x | x | x |

\*Applicable only to subjects who have chosen mental balance and sleep for behavior change

\*\* Applicable only to subjects who have chosen physical activity for behavior change

\*\*\* Applicable only to subjects who have chosen diet for behavior change

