## **1.6 Overall synopsis of the clinical investigation**

*Study design:* Post-market observational clinical investigation with a control group (a quasi-experimental study). The project also includes implementation and longitudinal studies.

*Inclusion criteria (intervention arms):* Adults  $\geq 18$  years who sign up for the service LongLife Active using BankID for identification, and consent to the research study.

*Inclusion criteria (controls):* Adults  $\geq 18$  years.

- *Exclusion criteria (intervention arms):* Individuals who are discharged from the app due to refracting the terms of the service will be excluded. Subjects scoring  $>70$  on well-being or subjects who appear as friends, colleagues, or family with anyone in the research or owner group will be excluded from the primary analyses.
- *Exclusion criteria (controls):* Age  $\leq 17$  years. Is currently using a digital product or any other kind of support for behavior change (e.g. Livsstilsverktyget, Health Integrator, Weight Watchers). Is found to be a user of LongLife Active. Subjects scoring  $>70$  on well-being or subjects who appear as friends, colleagues, or family with anyone in the research or owner group

will be excluded from the primary analyses.

*Number of subjects:* Intervention: 5000, Controls: 200

*Duration of the intervention:* the subjects will be followed up to 24 months.

*Follow-ups:* 3, 6, 12, 18, and 24 months

*Objectives:* The aim of this project is to evaluate the effectiveness of an individually tailored digital service aimed to support healthy habits on well-being among the adult population compared to a control sample of the general population.

Secondary objectives are to describe the internalization of the digital service, to evaluate the impact of the digital service on reaching self-identified goals, behavior change, and mental health, and to explore predicting and mediating factors for responses.

*Primary endpoint:* Well-being at 6 months

*Secondary (intermediate) endpoints:* Achieving self-identified goals, dietary and physical activity habits, and mental balance.

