### 3.3. Pre-clinical testing

A pilot study evaluating the feasibility of the digital service LongLife Active was completed in August 2022. The pilot study aimed to optimize the service to become usable and acceptable based on users' opinions. The subjects tested the service for three months. Validated questions on usability and acceptability of various functions were integrated into the service (30, 31) and engagement with the digital service have been evaluated by analysing analytics. The subjects were encouraged to leave continuous comments and feedback on the app by texting or speaking through a think-aloud function. Individual interviews and focus group discussions were arranged at the end of the test period to collect viewpoints on the digital service from users, health coaches, and program developers. A manuscript is in progress.

A total of 105 people showed an interest in participation, of these 55 participants signed up to use the digital service. Five participants dropped out due to various reasons, leaving 50 active users throughout the 12-week testing period. Most participants were recruited via social media (94%), most were female, and the majority were between the ages of 50-64. Regarding engagement with the app functions, 25 of the participants actively set at least one goal for behavior change. Most popular topic was physical activity, followed by mental balance and diet. The average goal success for both daily and weekly goals was 55.1%. In all, 39 participants had at least one activity from week 1 in the intervention period registered. In terms of engagement on a weekly basis with regards to registering activities, as expected fewer activities were registered later on in the intervention period; the number of activities registered dropped consecutively after week 5. Just over 80 activities were registered in week 1, with an increase to around 140 activities and staying steady at this level in weeks 2-5. This number then dropped to 60 activities in week 9 and further dropped to 20 activities in week 12. The most common (median) number of activities registered was 3. Across the 12-week intervention 14 participants wrote comments in the community function and 20 participants had at least one coaching session.

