#### *Exclusion criteria (controls):*

- age  $\leq 17$  years
- is currently using a digital product or any other kind of support for behavior change (e.g. Livsstilsverket, Health Integrator, Weight Watchers).
- is found to be a user of LongLife Active.
- subjects who appear as friends, colleagues or family with anyone in the research or owner group
- subjects scoring  $>70$  on well-being will be excluded from the primary analyses (36).

*Sample size:* The estimation is to reach 5000 consenting individuals in total for the intervention arms and 200 controls.

Total expected duration for each subject's participation: (intervention arms: 24 months, (controls)

*Drop-outs and discontinued use of the digital service:* Subjects who notify they would like to withdraw from the research study are disconnected to the data base. Subjects who discontinue using the digital service will be invited to continue the research participation and to answer the questionnaires online.

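### Goal achievement is taken only from app analytics, so it can follow logging rather than behaviour, and users who leave the app have no listed source for it

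*Protocol*

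**What the plan says.** The synopsis (Section 1.6) gives the secondary endpoints as "Achieving self-identified goals, dietary and physical activity habits, and mental balance". Under the heading Goal achievement, Section 6.3.2 says the endpoint will be "evaluated by collecting information on number of days/week the self-identified goal was met during the past month", and adds a confidence rating. It names no source for the number of days. Table 1 does: the row "Days/week the self-identified goal was met during the past month" has analytics in the instrument column and is scheduled at months 0, 1, 3, 6, 12, 18 and 24. Confidence is a separate row, at months 0, 3, 6, 12, 18 and 24. On sources in general, Section 6.3.2 states: "Data will primarily be collected through the app as self-reported answers to questionnaires and as analytics".

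On people who stop using the app, Section 6.2 says: "Subjects who discontinue using the digital service will be invited to continue the research participation and to answer the questionnaires online".

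Section 3.3 reports pilot registrations of about 140 activities a week in weeks 2-5. It continues: "This number then dropped to 60 activities in week 9 and further dropped to 20 activities in week 12".

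**The concern.** For a goal that the user must register by hand, app records show a goal-met day only if the user entered it. The variable is expressed per week over the whole past month, so it also covers days on which nothing was recorded. A person who keeps the habit but stops recording looks the same as a person who gave up the habit. A person who leaves the app but still answers questionnaires gives no value at all from the listed source.

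Three planned uses are exposed:

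- Objective III compares goal achievement across the three levels of support. Hypothesis 5, as I read it, expects engagement to level off in Basic and to hold in Standard and Premium. If logging follows engagement, a difference between levels can appear without any difference in behaviour.
- Objective V treats engagement as a mediator of goal achievement. Both are taken from analytics, so part of their association could come from the shared source.
- Objective VIII follows goal achievement to 24 months, well beyond the 12 weeks over which pilot logging fell.

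Hypothesis 4 also uses goal achievement as a mediator of later outcomes.

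**Working it through.** The protocol gives no sample size, power or expected value for goal achievement, so there is no planned figure to reproduce. The check is a comparison of passages, followed by an illustration of direction.

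**1. Is there a source for people who leave the app?** Section 6.2 keeps them in follow-up by online questionnaire. Table 1 lists only analytics for days the goal was met. The nearest questionnaire item is confidence, which is a different variable. As written, nothing listed in Table 1 captures the endpoint for them.

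**2. Is sparse logging foreseeable?** From the pilot counts in Section 3.3:

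- week 9 against weeks 2-5: 1 - 60/140 = 0.57, a fall of 57%
- week 12 against weeks 2-5: 1 - 20/140 = 0.86, a fall of 86%

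These are total activities across all users, not goal-met days per user. Some of the fall may be real loss of behaviour.

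**3. Does the coding of unlogged days matter?** Hold behaviour constant. For a level, take the pilot result: "The average goal success for both daily and weekly goals was 55.1" per cent. So p = 0.551, and true days per week = 7 × 0.551 = 3.86.

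*Unlogged counted as not met.* Recorded days = 7 × p × f, where f is the share of days logged. Assume f = 1 in weeks 2-5 and proportional to the pilot counts after that.

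| Logging level | f | Recorded days/week |
|---|---|---|
| Weeks 2-5 | 1 | 3.86 |
| Week 9 | 60/140 = 0.43 | 1.65 |
| Week 12 | 20/140 = 0.14 | 0.55 |

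With identical behaviour, two support levels with logging shares f1 and f2 would differ by 7p(f1 - f2). This is zero only if they log equally.

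*Unlogged counted as missing.* Recorded days = 7 × pr/(pr + 1 - p), where r is the chance of logging a met day divided by the chance of logging an unmet day. The values of r are assumptions.

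| r | Recorded days/week |
|---|---|
| 1 | 3.86 |
| 2 | 7 × 1.102/1.551 = 4.97 |
| 5 | 7 × 2.755/3.204 = 6.02 |

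One coding pulls the endpoint down. The other leaves it unchanged or pushes it up. Under missing coding, the dependence on logging disappears only when logging is unrelated to success (r = 1).

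**4. How far does engagement overlap?** Table 1 measures engagement by use of the action plan, attendance at community tutorials and coaching, and visits to the knowledge databases, all from analytics. Only the first is close to logging. The overlap is partial.

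**The case against.** The strongest reply is that the protocol nowhere says a day without an entry is a failure. Whether such a day is zero or missing is a derivation rule that can sit in the statistical analysis plan or the Case Report Form (Supplement 6), neither of which is shown. That is right. A reader might infer from the analytics source that unlogged days count as not met and that the endpoint must fall, but no passage supports this. What remains is a matter of collection: an analysis rule can choose a code for empty records, but it cannot recover an answer that was never requested.

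A reader might also infer that the text of Section 6.3.2 contradicts Table 1 by implying that the subject is asked. It does not. The text names no source, and the confidence rating may simply be a second variable.

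The pilot falls of 57% and 86% might be read as the size of the bias. They cannot be. The counts are pooled over users, only 25 participants set any goal, and 140 activities over 50 users is 2.8 per user per week, so weeks 2-5 are no proof of complete logging. The 55.1% may itself already count unlogged days as failures. The goal-setting function was also reworked after the pilot.

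Nor does the problem reach every goal: Section 2.1 allows physical activity to be registered automatically from a synced tracker or app. The claim that mediation by engagement could not be separated from goal achievement is also too strong, since two of the three engagement measures are not logging.

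Finally, self-report over a month is not clearly better than records made at the time, Section 7.4 calls the secondary outcomes exploratory, and the primary endpoint is untouched. These points limit the importance of the finding and argue for keeping both measures. They do not fill the gap for former users.

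**Conclusion.** The point holds in a limited form. Table 1 fixes analytics as the only listed source for a secondary endpoint, while Section 6.2 expects some subjects to continue without the app. For goals that rely on manual registration, the endpoint can move with logging rather than behaviour, and users who leave the app have no listed source. Part of an association with engagement (objective V), or of a difference between support levels (objective III), could therefore come from shared measurement.

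The size cannot be estimated from the documents, and the direction depends on an unstated coding. The figures above show direction under assumed logging shares and assumed values of r; they are not estimates of bias. The conclusion rests on Table 1 being complete. If Supplement 6 already holds a self-reported item, Table 1 only needs to list it. This is a change that should be made for the secondary and mediation analyses; it does not affect the primary well-being analysis.

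**What to change.** In Table 1 and under Goal achievement in Section 6.3.2:

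- Add a self-reported item on how many days a week the goal was met in the past month, beside the confidence question at months 0, 3, 6, 12, 18 and 24. Send it also to subjects who no longer use the app.
- Keep the analytics measure alongside it, and name both sources. Month 1, where confidence is not scheduled, stays with analytics alone.
- State that periods without any registration or synced data are not scored as goal not met.
- Report logging coverage by support level, so that the analytics measure can be read against it. A week with partial logging still understates goal-met days, which is a further reason to have the self-report.

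The cost is one more question in a questionnaire already sent, and a change to the extraction rule. Self-report may overstate success, and logged periods may be the better ones, so both measures should be shown.
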